### 8.3 Measuring malnutrition

Weight, height, MUAC and bilateral oedema will be measured upon inclusion and every following visit (scheduled and unscheduled). The nutritional status will be assessed using the weight-for-Height index according to the WHO 2006 growth standards, MUAC, and the presence of bilateral oedema.

Quality control will be ensured through: Training, Supervision and Evaluation, a guideline with standard procedures is added as annexe. Supervision will be done during all the study period and repeated training whenever be necessary for assuring good results.

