## **6.2 Blinding**

Owing to the nature of the product packaging and use of a control group without placebo study participants will not be blinded to which study group they were assigned. It will also not be possible to blind staff distributing the supplement.

Study staff blinded to the allocation treatment includes:

- Principle investigator
- Co-investigators
- Field Research Coordinator
- All clinical and ancillary medical staff
- Technical staff collecting anthropometric measurements
- Questionnaire interviewers
- Data managers
- Statisticians

Every effort will be made to ensure that study staff remains blinded to the treatment allocation. Efforts will be made to inform participants and staff to avoid discussion that might reveal allocation.

The allocation scheme will be formally revealed only after the data from the last participant has been captured.

Each participant will be assigned a unique study identification number, used to identify the study participant in all procedures. Study numbers will be assigned sequentially as subjects enter the study. Once a number has been assigned, that number will not be used again (e.g. if a subject discontinues or a number is allocated incorrectly).

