**Table 1: Schedule of study procedures**

| Procedure               | Day 0 | Day 14 | Day 28 and every 4 weeks after | Unscheduled visits | Final visit (day 168) |
|-------------------------|-------|--------|--------------------------------|--------------------|-----------------------|
| Informed consent        | √     | -      | -                              | -                  | -                     |
| Randomisation           | √     | -      | -                              | -                  | -                     |
| Baseline questionnaire  | √     | -      | -                              | -                  | -                     |
| Child health, history   | √     | √      | √                              | √                  | √                     |
| Clinical examination*   | √     | √      | √                              | √                  | √                     |
| Follow-up questionnaire | -     | √      | √                              | -                  | √                     |
| Weight                  | √     | √      | √                              | -                  | √                     |
| MUAC                    | √     | √      | √                              | -                  | √                     |
| Height                  | √     |        | √                              | -                  | √                     |
| DOT                     | √     | -      | -                              | -                  | -                     |
| RUTF / MNP distributed  | √     | √      | √ §                 | √ §     |                       |

|                          |   |   |   |   |   |
|--------------------------|---|---|---|---|---|
| Compensation distributed | √ | √ | √ | - | √ |
|--------------------------|---|---|---|---|---|

\* Complete exam when diagnosed with an illness or otherwise deemed necessary, otherwise limited to a rapid exam, including assessing treatment side-effects and response

§ When indicated

**Questionnaires:** Questionnaires will be translated into local languages, back-translated and piloted for comprehension in the area of the study site. (See annex f4 for baseline questionnaire and annex f5 for follow-up questionnaire)

**Unscheduled visits:** If unscheduled visit occurs within 48 hours prior to a scheduled visit, the child will not need to return for that upcoming scheduled visit.

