**Repeated supplementation:** Patients presenting with a new episode of a study disease will receive a new 14-day supplement, according to the intervention originally assigned. Though care and treatment will be available whenever ill, a child will not receive more than 14 days supplementation within any 28 day period. For example, a child receiving a new supplementation package on day-42 due to a newly diagnosed study disease cannot receive another supplementation package before day-70.

One reason to limit the distribution to a monthly frequency is to minimize potential bias related to the likelihood that children receiving Plumpynut® (a product known and recognized by the community) may be more likely to come forward for an unscheduled visit with the intention to receive additional distribution of supplementation.

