#### 8.3.2 Height

In order to detect even small increases in the height of a child, height will be measured at day-0 and every monthly visit to the clinic. Two (three) persons will use a precision height board (infant-child-adult measuring board, aluminium, Promes). One person will read out loud the height measured and the second person will verbally repeat the height for confirmation and record the result on the appropriate form.

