### **8.3.3 MUAC**

MUAC will be measured using an standard MUAC tape at day 0 and at the monthly visits. One person will read out loud the MUAC measurement and the second person will verbally repeat the measurement and record the result on the appropriate form.

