### **8.3.4 Oedemas**

Oedema will be evaluated applying pressure with thumb to top part of the foot for three seconds. If an oedema exists, an imprint will be left on the part of the foot where pressure was applied. The oedema must be observed on both feet, legs or could be generalised (always bilateral oedema) for considering the child has nutritional oedema. Oedema will be evaluated at day 0 and at monthly visits.

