## **8.8 Endpoints**

### **8.8.1 Primary endpoint**

The primary endpoint is “negative nutritional outcome (NNO)” of a child within the 6 months follow-up period. The incidence of a negative nutritional outcome will be defined according to the baseline nutritional status.

- i) for children with no malnourishment at time of entry into study, “negative nutritional outcome” is defined as progression to moderate or severe malnourishment

Thus, the event of a child reaching a “negative nutritional outcome” at least once within 6 months of follow-up period will be compared between the three study groups.

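### Section 8.3, Table 1 and sections 8.3.2 to 8.3.4 give different measurement schedules for the primary endpoint, so its detection can depend on unscheduled attendance, which may differ by arm

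*Protocol*

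**What the plan says.** Section 8.3 sets a broad rule: "Weight, height, MUAC and bilateral oedema will be measured upon inclusion and every following visit (scheduled and unscheduled".

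The neighbouring text differs:

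- **Table 1** carries a dash for weight, MUAC and height in the unscheduled-visit column. It ticks MUAC at day 14 and leaves height blank there.
- **Section 8.3.2:** "height will be measured at day-0 and every monthly visit to the clinic".
- **Section 8.3.3:** "MUAC will be measured using an standard MUAC tape at day 0 and at the monthly visits". Day 14 is not mentioned.
- **Section 8.3.4:** "Oedema will be evaluated at day 0 and at monthly visits".

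Section 8.8.1 makes the primary comparison one of a child "reaching a “negative nutritional outcome” at least once within 6 months of follow-up period will be compared between the three study groups", and section 9.3.1 counts the first occurrence over observed person-time. Neither section says which visits can supply the event.

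Three further statements bear on attendance. Section 6.2 says that "study participants will not be blinded to which study group they were assigned". The paragraph on repeated supplementation in section 8.2 says that children receiving RUTF "may be more likely to come forward for an unscheduled visit with the intention to receive additional distribution of supplementation", and gives this as one reason for limiting supply to 14 days in any 28. The note on unscheduled visits under Table 1 says: "If unscheduled visit occurs within 48 hours prior to a scheduled visit, the child will not need to return for that upcoming scheduled visit".

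**The concern.** When an event counts the first time it is seen, the number of looks is part of the endpoint. Under section 8.3 that number grows with unscheduled visits. Guardians decide on those visits, they know the allocation, and the visits fall when the child is ill and weight is likely to be low. If attendance differs by arm, detection differs by arm even when the true incidence is the same.

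Under Table 1 that route closes and a smaller one opens. A child seen ill within the 48 hours before a scheduled visit need not return, and the visit that took its place has no weight, MUAC or height. An endpoint assessment is then lost in a child who has just attended.

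Staff cannot follow all of these passages at once. What they do will decide which problem the trial has.

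**Working it through.** **1. The passages side by side**

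| Measure | Section 8.3 | Table 1, unscheduled | Table 1, day 14 | Sections 8.3.2 to 8.3.4 |
|---|---|---|---|---|
| Weight | every visit | no | yes | not covered |
| Height | every visit | no | blank | day 0, monthly |
| MUAC | every visit | no | yes | day 0, monthly |
| Oedema | every visit | no row | no row | day 0, monthly |

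Oedema may sit within the clinical examination that Table 1 ticks at unscheduled visits, since section 8.1 lists it there for day 0. For oedema the clear conflict is section 8.3 against section 8.3.4.

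**2. Reach of the 48-hour rule.** Scheduled visits after day 0 fall on days 14, 28, 56, 84, 112, 140 and 168. Seven windows of 2 days make 14 of 168 days, or 8.3%. About one in twelve unscheduled visits would fall in a replacement window if they were spread evenly (an assumption).

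**3. The plan's own figure.** Section 9.1 gives rates of 0.20 and 0.14, ratio 0.7, two-sided 0.05 and 80% power. The Poisson-regression formula with a balanced binary covariate gives

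N = [1.960 × √4 + 0.842 × √(2 + 2/0.7)]² / (0.20 × (ln 0.7)²) = 33.35 / 0.02544 = 1311,

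close to the stated 1320. Dropout: 660 / 0.90 = 733.3, so 734. The plan's sample size is reproduced.

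**4. Effect of extra looks.** The protocol gives no attendance rates, so these are assumed. Each affected child has one episode with uniform onset over 168 days and an exponential duration. It is detected if it covers a scheduled visit or if it triggers a measured unscheduled visit in its first 7 days. The trigger probability is 50% in control and 30% or 70% in RUTF. The control detected rate is held at 0.20 with 660 children per arm. The test statistic is ln(ratio)/SE, with SE² = (1−r₁)/(660r₁) + (1−r₀)/(660r₀). At 0.14 against 0.20 this gives 82% power, close to the plan's 80%.

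Short durations are included because section 1.5 cites recovery from diarrhoeal weight loss within 14 days. The 120- and 300-day rows are the 4 and 10 months of section 9.1.

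| Mean duration (days) | Detected, scheduled visits only | Detected at 30 / 50 / 70% | Ratio, no true effect, RUTF 30% / 70% | Chance of a significant result | Observed ratio if true ratio is 0.70 |
|---|---|---|---|---|---|
| 7 | 0.28 | 0.393 / 0.470 / 0.547 | 0.837 / 1.165 | 0.33 / 0.31 | 0.586 / 0.815 |
| 14 | 0.47 | 0.567 / 0.636 / 0.703 | 0.893 / 1.106 | 0.17 / 0.16 | 0.625 / 0.774 |
| 28 | 0.66 | 0.729 / 0.777 / 0.824 | 0.939 / 1.061 | 0.09 / 0.09 | 0.657 / 0.743 |
| 120 | 0.90 | 0.922 / 0.937 / 0.952 | 0.984 / 1.015 | 0.05 / 0.05 | 0.689 / 0.711 |
| 300 | 0.96 | 0.968 / 0.974 / 0.980 | 0.994 / 1.006 | 0.05 / 0.05 | 0.695 / 0.704 |

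Example, 14 days and 70%: 0.703/0.636 is 1.106 before rounding, so r₁ = 0.2212. SE = √(0.7788/146.0 + 0.80/132) = 0.1067 and z = 0.1007/0.1067 = 0.94. The two-sided chance of significance is Φ(−1.02) + Φ(−2.90) = 0.157.

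**The case against.** The strongest reply has five parts.

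- **The protocol does not predict higher RUTF attendance.** A reader might infer that it does. Its wording is conditional, and it appears where a countermeasure is being explained. This stands. The 28-day supply cap removes the motive for extra visits during part of follow-up. It does not limit attendance or measurement, because care stays available whenever the child is ill, so it is a partial remedy.
- **The direction is not fixed.** A reader might infer that extra RUTF visits would inflate RUTF events and hide a true benefit. Section 2 also sets out to test whether supplements reduce the three diseases. If they do, RUTF children would make fewer illness visits and the bias would favour RUTF. This stands.
- **Malnutrition that lasts months is caught at the next monthly visit anyway.** This stands for the durations in section 9.1, as the last two rows of the table show. It does not cover short illness-related dips.
- **The choice of visits that count belongs in the analysis plan, and the anthropometry staff are blinded.** The first part is fair for the analysis rule, but no analysis plan can recover a measurement that was not taken. Blinded measurers protect each reading, not the number of readings.
- **Sections 8.3.2 to 8.3.4 never say only, and Table 1 does not say that measurements are omitted at a replacing visit.** Both are true. The dashes in Table 1 are nevertheless explicit, and nothing shown adds measurements at a replacing visit. The follow-up form in the annex, which is not shown, may do so.

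**Conclusion.** The contradiction is literal, in current text, and concerns the data from which the primary endpoint is built. Under section 8.3, detection depends on unscheduled attendance, which may differ by arm. Under Table 1, the 48-hour rule can cost a scheduled assessment.

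The documents do not give the size. With assumed attendance of 30% to 70% in RUTF against 50% in control, the distortion is material for episodes of about 7 to 28 days: ratios of 0.84 to 1.17 down to 0.94 to 1.06 with no true effect. It is small at 4 and 10 months, within 0.98 to 1.02. No particular loss of power and no single direction of bias can be claimed. The point should be corrected because the ambiguity is cheap to remove and the protocol itself recognises the risk.

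**What to change.** 1. Reconcile section 8.3, Table 1 and sections 8.3.2 to 8.3.4 to one schedule, covering day 14 and giving oedema its own row. Which schedule to adopt is for the trial team.
2. Require weight, height, MUAC and oedema assessment at any unscheduled visit that replaces a scheduled one, and count it as that scheduled visit.
3. If other unscheduled visits keep anthropometry, record the visit type at which each NNO was detected and report unscheduled visits by arm. Analyse the primary endpoint both on the common scheduled grid and with all detections, naming in advance which is primary.
4. For the scheduled-grid analysis, state how a child first found malnourished at an unscheduled visit is counted. Section 8.7 withdraws and refers such a child, who may have recovered by the next scheduled visit. Assigning the event to the next scheduled visit would keep it, but would also carry the extra detection into that analysis. Report the number of such children by arm.

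The cost is wording, small form changes and one additional analysis. The sample size does not change.

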#### **9.3.1 Primary analysis of the primary endpoint**

The primary endpoint is “negative nutritional outcome” of a child within the 6 months follow-up period as defined in section 8.8.1. The incidence rate (in formulae below referred to simply as ‘rate’) of “negative nutritional outcome” will be computed as the number of events divided by total observed person-time in each treatment group. As an “event” the first time a child reaches a negative nutritional outcome will be used. The primary analysis of the primary endpoint will be performed on the intention to treat population with no imputation of missing data.

In the primary analysis, RUTF will be compared to the control group.  
The hypotheses in this step are

$$\begin{aligned} H_0: \text{rate}_{\text{RUTF}} &= \text{rate}_{\text{Control}} \\ \text{vs.} \\ H_1: \text{rate}_{\text{RUTF}} &\neq \text{rate}_{\text{Control}} \end{aligned}$$

where  $\text{rate}_{\text{RUTF}}$  = rate of “negative nutritional outcome” in the children in the RUTF group, and  $\text{rate}_{\text{Control}}$  = rate of “negative nutritional outcome” in the children in the control group.

The comparison of rates among the treatment groups will be performed by a Poisson regression model, adjusted for nutritional status at enrolment (fixed effect) and will be performed within one model including the three intervention groups with contrasts for each two-group comparison. Tests will be two-sided with a significance level of 0.05.

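### The protocol contradicts itself on whether nutritional status is measured at unscheduled visits, and the primary endpoint does not say which visits count, so detection of the endpoint could differ by arm

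*Protocol*

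**What the plan says.** **Measurement.** The opening of section 8.3 states that weight, height, MUAC and bilateral oedema "will be measured upon inclusion and every following visit (scheduled and unscheduled"), and that nutritional status is assessed from them. Table 1 has a dash for weight, MUAC and height in the unscheduled-visit column. The subsections agree with the table: "height will be measured at day-0 and every monthly visit to the clinic" (8.3.2), "MUAC will be measured using an standard MUAC tape at day 0 and at the monthly visits" (8.3.3) and "Oedema will be evaluated at day 0 and at monthly visits" (8.3.4).

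**Endpoint.** Section 8.8.1 says that reaching the NNO "at least once within 6 months of follow-up period will be compared between the three study groups". Section 9.3.1 adds that "the first time a child reaches a negative nutritional outcome will be used" as the event. Neither section says which visits can supply it.

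**Attendance.** Participants are not blinded (6.2), and guardians are told to bring the child whenever it is ill (8.2). The paragraph on repeated supplementation in 8.2 says that children receiving Plumpynut "may be more likely to come forward for an unscheduled visit with the intention to receive additional distribution of supplementation". It presents the 28-day limit as a response: "One reason to limit the distribution to a monthly frequency is to minimize potential bias".

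**The concern.** The chance of recording a first crossing of a threshold rises with the number of times the child is measured. Scheduled visits are the same in every arm. Unscheduled visits are started by guardians who know the allocation. If 8.3 governs, the number of looks at the primary endpoint can differ by arm for reasons unrelated to nutrition. Blinded measurers do not prevent this, because they do not decide when the child comes.

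The 28-day limit restricts how often product is issued. It does not restrict how often a child is seen and measured. The protocol has therefore named a source of differential attendance and addressed its effect on supplement use, but not its effect on detection of the primary endpoint.

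At stake is the RUTF-versus-control rate ratio, which is also the first step of the hierarchical test procedure. The contradiction also affects which data are collected, and measurements taken inconsistently cannot be repaired at analysis.

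**Working it through.** **1. What is measured at an unscheduled visit**

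| Place | Weight | Height | MUAC | Oedema |
|---|---|---|---|---|
| 8.3, opening | yes | yes | yes | yes |
| Table 1 | no | no | no | no separate row |
| 8.3.2 | | day 0, monthly | | |
| 8.3.3 | | | day 0, monthly | |
| 8.3.4 | | | | day 0, monthly |

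One sentence stands against the table and three subsections. Day 14 is also unsettled: Table 1 has weight and MUAC there but leaves height blank, while 8.3.3 and 8.3.4 do not list day 14.

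**2. The plan's own sample size (9.1)**

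Inputs: rates 0.20 and 0.14 (ratio 0.70), two-sided 0.05, 80% power, equal allocation. Poisson regression with a binary covariate:

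N = (z₁·√V₀ + z₂·√V₁)² / (μ·(ln RR)²), with V₀ = 1/(0.5 × 0.5) = 4 and V₁ = 1/0.5 + 1/(0.5 × 0.7) = 4.857.

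N = (1.960 × 2 + 0.842 × 2.204)² / (0.20 × 0.1272) = 33.35 / 0.02544 ≈ 1311.

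The plan states 1320, at which power is 80.3%. For dropout, 660/0.9 = 733.3, which rounds up to 734. The plan's figures reproduce.

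**3. A simple bound**

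There are 7 scheduled follow-up assessments (days 14, 28, 56, 84, 112, 140, 168). Assumptions, since the documents give no figures: u = 2 unscheduled visits per child in every arm, e extra visits per RUTF child, and a share s of events that depends on the number of looks.

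Observed RR = 0.70 × (1 + s·e/(7 + u))

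| s | e = −1 | e = +1 | e = +2 |
|---|---|---|---|
| 0.25 | 0.68 | 0.72 | 0.74 |
| 0.5 | 0.66 | 0.74 | 0.78 |
| 1 | 0.62 | 0.78 | 0.86 |

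The last row is an outer limit: every event would have to depend on the number of looks.

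**4. Simulation by length of episode**

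Episodes have exponential length and are detected only if a visit falls inside one. Onset rates are calibrated so that scheduled visits alone detect 0.20 and 0.14. Unscheduled visits are Poisson in number and spread evenly over 168 days, with a mean of 2 in control. Entries are the ratio of proportions ever detected, with power at 1320 in brackets.

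| Mean episode | Scheduled only | Equal visits | RUTF +1 | RUTF +2 | RUTF −1 |
|---|---|---|---|---|---|
| 7 days | 0.707 (78%) | 0.706 (83%) | 0.742 (71%) | 0.778 (58%) | 0.670 (91%) |
| 14 days | 0.699 (80%) | 0.698 (83%) | 0.718 (78%) | 0.741 (70%) | 0.674 (89%) |
| 30 days | 0.697 (81%) | 0.706 (80%) | 0.720 (76%) | 0.723 (75%) | 0.689 (85%) |
| 120 days | 0.694 (82%) | 0.700 (81%) | 0.695 (82%) | 0.705 (79%) | 0.696 (82%) |

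The scheduled-only column should read 0.70 throughout, so differences of about 0.01 are simulation noise. Equal visit numbers leave the ratio alone. Unequal numbers move it in either direction. Episodes of 120 days, the 4 months that 9.1 assumes for severe malnutrition, leave almost nothing to distort, because a later scheduled visit usually finds them.

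**The case against.** The strongest case against has four parts.

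**8.3 may not be the operative rule.** It says measured, not scored, and Table 1 and three subsections point the other way. This stands. The firm error is the contradiction together with an endpoint that leaves the qualifying visits open. It is not a settled decision to score unscheduled visits.

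**Extra attendance is only a possibility.** The protocol says it may happen. Supplement also requires a newly diagnosed study disease, and malaria and LRTI are confirmed by a rapid test and a respiratory rate. This lowers the incentive. It does not remove it, since diarrhoea is defined by stool frequency, and a visit that earns no product would still be a measured visit under 8.3.

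**The direction is open.** The trial hypothesises that supplementation reduces illness. RUTF children might then make fewer sick visits, which would exaggerate the benefit. This stands.

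**The size depends on short-lived crossings.** Section 9.1 assumes durations of 4 and 10 months. This also stands, although brief illness dips and readings near the cut-off can produce short crossings.

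A reader might infer that RUTF will certainly be over-detected and that power will fall to roughly a third to a half. Figures of that kind (ratio 0.76 to 0.84) arise if weight-for-height z fluctuates independently from visit to visit, RUTF children make 50 to 100% more unscheduled visits, and each such visit carries a 0.2 z illness dip. The documents support none of these inputs. A visit made to obtain product also need not be a visit at the child's lightest. Without the dip, that model gives 0.72 to 0.76. With fluctuations correlated over 120 days and no dip, doubling RUTF visits moves the ratio only from 0.67 to 0.69.

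**Conclusion.** The point holds as a contradiction with a conditional consequence. The protocol disagrees with itself on whether nutritional status is measured at unscheduled visits, and the primary endpoint counts the first NNO without limiting the visits that can supply it. If 8.3 is followed, detection of the primary endpoint can depend on attendance, which may differ by arm in a trial whose participants are unblinded.

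No size can be derived from the documents. With 2 unscheduled visits in control, 1 to 2 more under RUTF and episodes averaging 7 to 30 days, a true ratio of 0.70 reads about 0.72 to 0.78, with power about 58% to 78%. With 120-day episodes there is almost no change. With one fewer RUTF visit the ratio reads about 0.67 to 0.70. If the site follows Table 1, the bias largely disappears.

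This should be fixed. The remedy does not depend on the direction, since it removes arm-dependent detection either way.

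**What to change.** 1. Reconcile the opening of 8.3 with Table 1 and 8.3.2 to 8.3.4, so that one rule states what is measured at unscheduled visits and at day 14.
2. State in 8.8.1 and 9.3.1 that the primary NNO is determined only from measurements at scheduled visits common to all arms at which the needed measurements are taken: day 28 and every 4 weeks to day 168. Include day 14 only if the passages are reconciled on height, MUAC and oedema at that visit.
3. Let an unscheduled visit within the existing 48-hour window count as the scheduled visit it replaces, with that visit's measurements taken. Table 1 as it stands would leave them out.
4. Do not score a child as an event because of referral or feeding-programme treatment that followed an unscheduled measurement. Section 8.7 refers every child found malnourished, so such a rule would bring the extra detections back. In the independent-fluctuation model (0.2 z dip, 1.5 versus 3 visits, all referred children assumed in treatment at the next scheduled date) the ratio is 0.68 with scheduled visits only, 0.81 with all visits, and 0.82 with referrals counted.
5. Say that scheduled measurements taken after a withdrawal for malnutrition are used. Section 8.7 continues follow-up where possible but leaves use of the data to the statistician.
6. Report the all-visit definition, including referrals between scheduled visits, as a sensitivity analysis, and unscheduled visits per child by arm.

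The cost is wording; care and referral are untouched. There is a small downside: some events found between scheduled visits, including children who recover after referral, count only in the sensitivity analysis. Recovery of that kind could also differ by arm, which is why the sensitivity analysis is needed.
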